### Sample size

Calculation of the sample size of this trial was based on the effect size of the primary outcome, Eczema Area and Severity Index (EASI) score, reported in a previous published study [18]. The means and standard deviations (SDs) of the EASI scores were 7.4 ± 3.3 and 9.6 ± 4.1 for the active treatment and control groups, respectively. To achieve 90 % power (β = 0.10), significance level of 0.05 (α) in a two-tailed test, calculated by using G*Power 3.1.2 (http://www.gpower.hhu.de/en.html), 62 participants, based on an estimated 10 % dropout rate, are needed for each group. That makes a total of 124 for the main trial. A pilot study with 30 participants (15 per group) conducted in RMIT University will provide preliminary data on the clinical efficacy of PTQX based on EASI score and will allow us to monitor for adverse events. The mean and SD of EASI score from the pilot study will be used for recalculation of the sample size for the main trial.

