## Methods/Design

The trial will be a 16-week, randomised, double-blind, placebo-controlled, two-arm, parallel clinical trial. The 16-week trial includes 12 weeks of treatment with either PTQX or placebo and a 4-week follow-up period. Figure 1 outlines the process of the trial. A pilot study (*N* = 30) will be conducted to inform a planned larger RCT (*N* = 124). The study protocol was approved by the Royal Melbourne Institute of Technology (RMIT) University Human Research Ethics Committee (HREC), filed with the Therapeutic Goods Administration (TGA) under the Clinical Trial Notification (CTN) scheme (CTN file number: 2014/033590) and registered with the Australian and New Zealand Clinical Trials Registry (ANZCTR) (registration ID: ACTRN12614001172695; dated 7 November 2014).

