### Randomisation

A block randomisation method will be employed with balanced variable blocks. Equal numbers of participants will receive the real treatment and the inert vehicle (the placebo). Randomisation codes will be generated by a computer program run by an independent statistician who is not directly involved with the trial.

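### The 62 per group said to allow for 10 % dropout matches the requirement with no dropout; a 10 % allowance at 90 % power would correspond to 69 per group

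*Protocol article*

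**What the plan says.** The Sample size section takes its effect from an earlier published study: "The means and standard deviations (SDs) of the EASI scores were 7.4 ± 3.3 and 9.6 ± 4.1" for active treatment and control respectively. It asks for 90 % power with a "significance level of 0.05 (α) in a two-tailed test", "calculated by using G*Power 3.1.2". The result is that "62 participants, based on an estimated 10 % dropout rate, are needed for each group", followed by "That makes a total of 124 for the main trial". The Randomisation section sets equal allocation: "Equal numbers of participants will receive the real treatment and the inert vehicle (the placebo".

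Three other statements bear on the point:

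- The section on withdrawal, dropout and discontinuation says that discontinuers are not replaced. Their missing data are to be handled by last observation carried forward (LOCF) within an intention-to-treat analysis.
- The same section offers those who stop the trial medication continued outcome visits.
- The Sample size section says that the pilot mean and SD of EASI will be used to recalculate the size of the main trial.

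**The concern.** The sentence presents 62 as a figure that already contains the dropout allowance. If so, the calculation before inflation should have given about 56 per group, since 62 × 0.9 = 55.8. The printed means and SDs do not lead to 56 at 90 % power. They lead to 62. The sample size, the power and the dropout allowance therefore cannot all be right together.

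What is at stake is the planned power for the primary outcome. Neither the type I error nor any treatment estimate is affected. There is also a forward risk: if the recalculation from the pilot follows the same steps, the main trial's final size would again lack the allowance that the text claims.

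**Working it through.** **Inputs, all from the Sample size section unless noted.** Means 7.4 and 9.6; SDs 3.3 and 4.1; two-sided alpha 0.05; power 0.90; dropout 10 %; 62 per group, 124 in total. Allocation is 1:1 (Randomisation). The software is named but the test is not, so a two-sample t test is assumed.

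**Step 1: effect size.**

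- Difference = 9.6 − 7.4 = 2.2
- Pooled SD = √[(3.3² + 4.1²)/2] = √[(10.89 + 16.81)/2] = √13.85 = 3.722
- d = 2.2/3.722 = 0.591

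**Step 2: reproduce the plan's figure.** Power comes from the noncentral t distribution with 2n − 2 degrees of freedom and noncentrality d√(n/2).

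| n per group | Power |
|---|---|
| 55 | 86.7 % |
| 56 | 87.3 % |
| 61 | 89.9 % |
| 62 | 90.4 % |
| 69 | 93.2 % |

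The smallest n that reaches 90 % is 62, with every participant evaluable. The normal approximation gives 61.

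**Step 3: apply the stated allowance.** 62/(1 − 0.10) = 68.9, so 69 per group and 138 in total. Starting from 61, the normal approximation gives 61/0.9 = 67.8, so 68 per group and 136 in total. Neither is 62.

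**Step 4: look for another reading that gives 62 after inflation.** At two-sided 0.05 and 90 % power:

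| SD used | n before inflation | n after 10 % |
|---|---|---|
| 3.7 (simple average) | 61 | 68 |
| 4.1 in both arms | 74 | 83 |
| 3.3 in both arms | 49 | 55 |

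A one-sided test with the pooled SD gives 50, inflated to 56. The only match found is SD 4.1 in both arms at 80 % power by the normal approximation (55, inflated to 62). That contradicts the stated power and one of the stated SDs.

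**Step 5: what 62 randomised per group gives if 10 % drop out.**

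- *Completers only:* 62 × 0.9 = 55.8, about 56 per group. Power is 87.3 %, so beta is about 0.13 against the stated 0.10.
- *All 62 analysed, as the LOCF plan implies:* let dropouts retain a fraction f of the effect, with SDs unchanged (an assumption). The average difference is 2.2 × (0.9 + 0.1f).

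| f | Average difference | Power at 62 per group |
|---|---|---|
| 1 | 2.20 | 90.4 % |
| 0.5 | 2.09 | 87.3 % |
| 0 | 1.98 | 83.6 % |

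**The case against.** Four things can be said for the plan.

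**LOCF keeps everyone in.** The protocol plans to analyse all randomised participants, so no one is lost from the denominator and 62 may be all that is needed. It is true that 87 % describes an analysis of completers, which is not the planned one. But Step 5 shows that 90 % is held only if carried-forward values keep essentially the full difference. The sentence also claims a dropout allowance, which LOCF does not supply.

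**124 is not final.** The Methods/Design section says the pilot "will be conducted to inform a planned larger RCT", and the size is to be recalculated. This stands. A reader might infer that the main trial will fall short of 90 % power. The document does not support that, because the final number will come from new inputs. What it supports is that the number printed now disagrees with its own inputs.

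**The test is not named.** That no inflation was applied is an inference. The t-test match is exact and no variant of the stated inputs gives 62 after inflation, so the inference is strong. It remains a match to the uninflated figure and not a record of what was done.

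**Baseline adjustment would recover the loss.** Baseline EASI is collected at visit 1, and adjusting for it may raise power. A reader might go on to infer that adjustment restores 90 % at 124. With 56 per group and a baseline to week-12 correlation of 0.3, the residual variance falls by a factor of 1 − 0.3² = 0.91 and power is 90.2 %. The document gives no such correlation, and the calculation also assumes that the quoted SDs are those of post-treatment scores. The claim cannot be made from this document.

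**Conclusion.** The statement is wrong as written. On the stated inputs, 62 per group is the two-sample t-test requirement with no dropout, and the claimed 10 % allowance is not in it. The gap is 7 per group, or 14 in total (138 − 124).

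In terms of power the gap is modest: 87.3 % against 90 % for completers, or about 84 % to 90 % with all 62 analysed. These figures rest on the quoted means and SDs, 1:1 allocation, a two-sample t test and exactly 10 % dropout. The 84 % to 90 % range also assumes unchanged SDs and dropouts who retain between none and all of the effect.

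This is an arithmetic correction to a provisional planning figure. It does not show that the completed main trial will be underpowered.

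**What to change.** Replace the sentence with one that separates the three quantities:

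- 62 per group gives 90 % power with no loss.
- With 10 % dropout, about 56 completers per group give about 87 % power. Label this as a completers-only figure, and add that under the planned intention-to-treat analysis with LOCF, power is about 84 % to 90 % if dropouts retain none to all of the effect and SDs are unchanged.
- A 10 % allowance at 90 % power corresponds to 69 per group, 138 in total.

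In the recalculation from the pilot data, report the number per group before inflation, the dropout rate and the number after dividing by one minus that rate, each on its own line. Baseline adjustment may be mentioned as a possible source of extra power, but not as restoring 90 % unless a correlation is available to support it.

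The cost is one corrected sentence and one explicit step in a recalculation already planned. No extra participants are needed if the power is restated. Holding 90 % with the allowance on the current inputs would take 14 more.

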### Statistical analysis

Data will be analysed by an independent statistician using IBM SPSS version 22 software (IBM, Armonk, NY, USA). Comparison of means of continuous variables (i.e., EASI, POEM and CDLQI scores) will be expressed as differences in means with 95 % confidence intervals (CIs). One-way analysis of variance will be used for normally distributed data, and nonparametric tests will be used for skewed distribution data. χ^2^ or Fisher’s exact tests will be performed for comparison of dichotomised data, and dichotomous data will be expressed as risk ratios with 95 % CIs. All comparisons will be two-tailed, with *p* values <0.05 considered to be statistically significant.

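### Recalculating the main-trial size from the pilot's EASI means lets a 15-per-group difference, with a standard error of about 1.36 points, replace the 2.2-point planning difference

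*Protocol article*

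**What the plan says.** The Sample size section of the protocol article bases the main trial on the EASI effect "reported in a previous published study": "The means and standard deviations (SDs) of the EASI scores were 7.4 ± 3.3 and 9.6 ± 4.1 for the active treatment and control groups, respectively". With 90% power and a "significance level of 0.05 (α) in a two-tailed test", it arrives at 62 per group and 124 in total, and says this allows for 10% dropout.

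It then describes a pilot of 30 children, 15 per group, which "will provide preliminary data on the clinical efficacy of PTQX based on EASI score", and closes with the rule at issue: "The mean and SD of EASI score from the pilot study will be used for recalculation of the sample size for the main trial".

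The opening of Methods/Design adds only that the pilot is to inform the larger trial. The article gives no difference to be held fixed, no lower or upper limit on the new size, and no allowance for the pilot's imprecision.

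**The concern.** A pilot of this size can say something useful about the SD and dropout. It says very little about the treatment difference. Required sample size varies with the inverse square of that difference, so sampling error in it is magnified. A pilot that overstates the effect by chance shrinks the main trial below what it needs. One that understates the effect inflates the trial or leaves no computable size. Either can happen when the true effect is exactly what was planned.

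What is at stake is the aim stated in the article's own Abstract, an adequately powered trial in a field where such trials are lacking. This is not a detail left to a later document. It is a stated rule that determines how large the main trial will be.

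**Working it through.** **Inputs (Sample size section).** Means 7.4 and 9.6, SDs 3.3 and 4.1, two-sided alpha 0.05, power 90%, dropout 10%, pilot 15 per group. Allocation is equal (Randomisation section).

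**1. The plan's own figure.**
- Difference = 9.6 − 7.4 = 2.2.
- Pooled SD = √[(3.3² + 4.1²)/2] = 3.722, so d = 2.2/3.722 = 0.591.
- Normal approximation: n = 2 × (1.960 + 1.282)² × 3.722²/2.2² = 60.1, rounded up to 61 per group. The t-test calculation gives 62.
- So 62 reproduces as the number of evaluable children before dropout. With 10% dropout, 62/0.9 = 68.9, or 69 per group and 138 in total. If 62 are recruited and 10% are lost, about 56 remain and power is about 87%. This matters below because it sets the right floor.

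**2. Precision of the pilot difference.**
- SE = 3.722 × √(2/15) = 1.36 points.
- Expected 95% interval (t with 28 df, 2.048): 2.2 ± 2.78, or about −0.6 to 5.0.
- Chance of a zero or reversed difference when 2.2 is true: Φ(−2.2/1.36), about 5%.
- Power of the pilot itself: about 35%.

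**3. One standard error either way, with the SD as planned.**

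| Pilot difference | n per group (evaluable) | Total with 10% dropout | Power if 2.2 is true |
|---|---|---|---|
| 2.2 + 1.36 = 3.56 | 24 | 54 | 52% |
| 2.2 − 1.36 = 0.84 | 413 | 918 | near 100% |

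**4. Full distribution.** 200,000 pilots were simulated with 15 per group, normal data and the means and SDs above. Each was used to recalculate n for 90% power (t-test, before dropout). True power was then evaluated at d = 0.591.

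| Result | Pilot difference and SD | Pilot SD only, 2.2 fixed |
|---|---|---|
| Middle 50% of n per group | about 30 to 178 | about 50 to 72 |
| 5th percentile | 15 | about 37 |
| 95th percentile | no solution | about 91 |
| 31 or fewer per group | about 27% | about 1% |
| More than 124 per group, or no solution | about 31% | about 0.1% |
| True power below 80%, where n exists | about 42% | about 16% |
| True power below 70%, where n exists | about 34% | about 4% |

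SD-only updating has mean power of about 88%. With a floor of 62 evaluable per group, power stays at or above 90% in every run.

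**5. Why the SD behaves better.** With 28 df the 95% interval for the SD is about 2.95 to 5.03, or 0.79 to 1.35 times the estimate. The corresponding factor on n is 0.63 to 1.83. The difference, by contrast, has an interval that includes zero.

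**6. Other true differences.** When the pilot difference is used and the true difference is 1.5, about 43% of pilots lead to power below 80% and 39% to a total above 500 or no solution. At 3.0 the figures are about 36% and 9%. The instability does not depend on 2.2 being exactly right.

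**The case against.** **The text does not spell out a substitution.** It says the pilot's mean and SD will be used, not that the between-group difference mechanically replaces 2.2, and a fuller protocol may hold an operating rule. This stands as a limit on the figures, which describe a literal application with no floor, cap or judgement. It does not remove the point. The same section sized the trial from group means and SDs and says the pilot will yield efficacy data, and naming the mean would be needless if only the SD were intended.

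**The planning difference is itself one study's observed result.** This stands. The article does not call 2.2 clinically important and does not give the earlier study's size. If the truth is 1.5, even 62 evaluable per group has only about 61% power. So the power figures for the fix are conditional on 2.2, and the target needs a justification. It would be too strong to say that a pilot carries no information on the effect. It carries too little to size a trial.

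**Stronger readings.** A reader might infer that the recalculation inflates the type I error, or that comparing the arms breaks a needed blind, because the same children feed both the recalculation and the final test. The article does not support this. It describes a separate pilot of 30 beside a main trial of 124 and nowhere says pilot children enter the main analysis. Comparing arm means after a separate pilot is ordinary practice.

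**Conclusion.** The concern holds as a problem of imprecision. On the natural reading, a difference with a standard error of 1.36 points would decide the size of a trial planned around 2.2 points. Applied literally with the planning values true, it gives about a two-in-five chance of true power below 80% where a size can be computed. It also gives about a three-in-ten chance of more than double the planned 62 per group, or no size at all.

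These figures assume normal data, an unadjusted comparison of EASI scores and no judgement overriding the result. The pilot's own randomisation and analysis are unaffected, and 124 stands until someone recalculates. The sentence can therefore be corrected before the main trial, and should be corrected before pilot results are seen by group.

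**What to change.** Replace the last sentence of the Sample size section with a rule to this effect:

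- The target difference is prespecified and held fixed at 2.2 EASI points, or at another value that the sponsor justifies as clinically relevant before seeing pilot results.
- Only the pilot's pooled within-group SD and its dropout rate update the size. Optionally, use the one-sided upper 80% confidence limit of the SD, √(28/χ²) with the 20th percentile of χ² on 28 df, about 1.14 times the estimate. The pooled within-group SD needs group labels and should not be described as blinded, because a blinded SD would absorb the treatment difference.
- The size does not fall below 62 evaluable per group, about 69 recruited with 10% dropout.
- The pilot's efficacy difference is reported descriptively, with its interval.

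The edit is one sentence and the pilot is unchanged. There are two costs. A favourable pilot can no longer shrink the main trial, and the dropout-corrected floor is 138 in total instead of 124, 14 more children. The floor is needed: without it, SD-only updating still leaves about 16% of cases below 80% power.

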### Screening and run-in, baseline, treatment periods and endpoint

Preliminary screening assessments will be conducted during the 2 weeks of the run-in period (weeks −2 and −1). Only those participants who have met the inclusion and exclusion criteria will be randomised. EASI score and other baseline outcome assessments will be measured.

The treatment period will involve oral ingestion of the trial medications twice daily for 12 weeks. The trial medications will be supplied to participants at visit 1 (week 0), visit 2 (week 4) and visit 3 (week 8). The endpoint is set at visit 4 (week 12) of the trial period.

### Outcome measures

Current recommendations for outcome measurement in RCTs of AE include clinical signs and symptoms, long-term control of flares and health-related QoL [19]. This trial will adopt these recommendations for its outcome measures. The primary outcome measure is change in clinical signs severity based on EASI score. Secondary outcome measures include change in symptoms using the Patient-Oriented Eczema Measure (POEM) [20], health-related QoL using the Children’s Dermatology Life Quality Index (CDLQI) [21], use of concomitant medicines (number of days used and total dosage for corticosteroids) and adverse events and safety (pathology tests).

The EASI, POEM, CDLQI, concomitant medications and adverse events will be recorded at visit 1 (week 0), visit 2 (week 4), visit 3 (week 8), visit 4 (week 12) and visit 5 (week 16). Pathology tests (full blood examination with eosinophil count and immunoglobulin E, liver and renal function tests) will be performed by a qualified phlebotomist at the screening (week −2) and at the second (week 4) and fourth (week 12) visits. Medical advice from a medical officer will be sought for any serious adverse events or for any serious aggravation of the existing skin condition or abnormal pathology results during the trial period.

Any adverse events will be managed in compliance with the guidelines of the *Note for Guidance on Clinical Safety Data Management: Definitions and Standards for Expedited Reporting (CPMP/ICH/377/95)* issued by TGA [22]. A serious adverse event will be reported to the RMIT HREC within 24 hours and then to the TGA within 7–15 days. Table 1 summarises the schedule of the trial and outlines the time points of outcome measures of the trial.

**Table 1 Tab1:** Schedule of the trial

Items	Screening/run-in period	Visit 1 (baseline)	Visit 2	Visit 3	Visit 4 (endpoint)	Visit 5 (follow-up)
Week of the trial	−2/−1	0	4	8	12	16
Demographic information-taking	+					
Informed consent form (PICF)	+					
General medical history-taking	+					
Severity of AE for inclusion and exclusion of the participants (NESS)	+					
Blood tests	+		+		+	
Clinical sign of AE (EASI)		+	+	+	+	+
Symptoms (POEM)		+	+	+	+	+
QoL score (CDLQI)		+	+	+	+	+
Distributions of treatment or placebo products		+	+	+		
Daily medical record	+	+	+	+	+	+
Monitor of adverse event		+	+	+	+	+
Compliance check		+	+	+	+	+
Survey of participation						+

*Abbreviations: AE* atopic eczema, *CDLQI* Children’s Dermatology Life Quality Index, *EASI* Eczema Area and Severity Index, *NESS* Nottingham Eczema Severity Score, *PICF* participant information and consent form, *POEM* Patient-Oriented Eczema Measure, QoL quality of life

### Statistical analysis

Data will be analysed by an independent statistician using IBM SPSS version 22 software (IBM, Armonk, NY, USA). Comparison of means of continuous variables (i.e., EASI, POEM and CDLQI scores) will be expressed as differences in means with 95 % confidence intervals (CIs). One-way analysis of variance will be used for normally distributed data, and nonparametric tests will be used for skewed distribution data. χ^2^ or Fisher’s exact tests will be performed for comparison of dichotomised data, and dichotomous data will be expressed as risk ratios with 95 % CIs. All comparisons will be two-tailed, with *p* values <0.05 considered to be statistically significant.

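### The EASI outcome, its test and its sample-size SD are not tied to one quantity, and the named test does not adjust for baseline EASI

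*Protocol article*

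**What the plan says.** Four sections of the protocol article bear on this point.

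- Outcome measures: "The primary outcome measure is change in clinical signs severity based on EASI score".
- Sample size: "The means and standard deviations (SDs) of the EASI scores were 7.4 ± 3.3 and 9.6 ± 4.1" in the active and control groups of a published study. No SD of change and no correlation with baseline is given. The main-trial size is to be recalculated from the pilot mean and SD of the EASI score.
- Statistical analysis: "Comparison of means of continuous variables (i.e., EASI, POEM and CDLQI scores) will be expressed as differences in means". For the test, "One-way analysis of variance will be used for normally distributed data", and "nonparametric tests will be used for skewed distribution data". No covariate is named.
- Screening and run-in, baseline, treatment periods and endpoint: "EASI score and other baseline outcome assessments will be measured", and "The endpoint is set at visit 4 (week 12) of the trial period". Table 1 shows EASI, POEM and CDLQI all recorded at week 0.

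**The concern.** The outcome is a change, the sample size rests on the spread of scores, and the analysis section refers to scores without a time point. A week-12 score and a change from baseline have different variances, so the stated 90 % power applies to one and not, in general, to the other.

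A one-way ANOVA has a single factor and no covariate. On either variable it gives up precision that the week-0 EASI could supply. This matters more because the mismatch can carry forward: if change is what is analysed, a recalculation from the pilot SD of the score would set the main-trial size from the wrong SD.

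The analysis section names the test itself, so this is not simply detail left to an analysis plan.

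**Working it through.** **Inputs from the Sample size section.** Means 7.4 and 9.6; SDs 3.3 and 4.1; two-sided alpha 0.05; power 90 %; 62 per group.

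**Inputs not in the document (assumed).** The correlation r between baseline and week-12 EASI is taken as 0.3 to 0.7, with r = 0 as a limiting case. The SDs at baseline and week 12 are taken as equal.

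**Step 1: the plan's own figure.**
- Difference = 9.6 − 7.4 = 2.2.
- Pooled SD = √[(3.3² + 4.1²)/2] = √[(10.89 + 16.81)/2] = √13.85 = 3.722.
- Standardised effect = 2.2/3.722 = 0.591.
- A two-sample t-test (noncentral t) needs 62 per group and has 90.4 % power at that size.

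So 62 reproduces as the number for an unadjusted comparison of scores, before any dropout. (With the stated 10 % dropout it would be 62/0.9, rounded up to 69. That is a separate matter, but it means the plan has no slack.)

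**Step 2: SD of each candidate analysis.** With s = 3.722:
- score: s
- change from baseline: s√[2(1 − r)]
- ANCOVA residual: s√(1 − r²), with one degree of freedom lost

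The change SD equals s when 2(1 − r) = 1, that is at r = 0.5. Below that value the change is noisier than the score.

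**Step 3: power at 62 per group, true difference 2.2.**

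| r | SD of change | ANCOVA SD | Change | Score | ANCOVA |
|---|---|---|---|---|---|
| 0 | 5.263 | 3.722 | 63.6 % | 90.4 % | 90.4 % |
| 0.3 | 4.403 | 3.550 | 78.8 % | 90.4 % | 92.8 % |
| 0.5 | 3.722 | 3.223 | 90.4 % | 90.4 % | 96.5 % |
| 0.7 | 2.883 | 2.658 | 98.8 % | 90.4 % | 99.5 % |

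**Step 4: number per group for 90 % power, before dropout.** Change: 86 at r = 0.3, 74 at r = 0.4, 62 at r = 0.5, 38 at r = 0.7. ANCOVA: 56 at r = 0.3, 47 at r = 0.5, 32 at r = 0.7.

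**Step 5: with about 10 % lost (62 × 0.9 = 55.8, so 56 per group).** The unadjusted score comparison has 87.3 % power. ANCOVA has about 90 % at r = 0.3 and 94.7 % at r = 0.5.

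**Step 6: why ANCOVA settles score versus change.** Write change as Y − B, with Y the week-12 score and B the baseline. Regressing Y or Y − B on treatment and B gives models that differ only in the coefficient of B, which shifts by exactly 1. The treatment coefficient and its standard error are identical.

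**The case against.** The strongest reply is that nothing here is invalid. Allocation is randomised 1:1, so an unadjusted comparison is unbiased and its confidence interval already allows for chance imbalance at baseline. On scores, the plan keeps its 90 % at every r. This stands: the loss is in precision and clarity, and a reader who infers bias goes further than the document allows.

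Other stronger readings also fail:

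- **That the analysis ignores baseline EASI.** This is certain only if week-12 scores are compared. If change is compared, baseline enters by subtraction and only covariate adjustment is missing. The document does not say which.
- **That the sample size used end-of-treatment SDs.** The section calls them only EASI scores. What can be said is that they are not described as SDs of change.
- **That the trial is underpowered.** The shortfall in the change analysis is confined to low r; at r = 0.7 change exceeds the plan. The threshold of 0.5 also needs equal SDs. If the baseline SD is k times the week-12 SD, the variance of change is s²(1 + k² − 2rk) and the threshold becomes r = k/2. The document gives no baseline SD.
- **That adjustment always gains and is free.** It gains nothing at r = 0 and costs one degree of freedom, although that is under 0.1 percentage point of power at 124 participants.

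The main-trial size is provisional, so power at 62 per group is not final. But the recalculation is itself specified on the score SD, so it does not resolve the question. Covariates are often left to an analysis plan. That defence is only partial, because this section fixes a test that has none. Finally, the power figures apply to the normal-data branch only.

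**Conclusion.** The point holds as a recommendation to change the plan, not as an error that invalidates it. The outcome definition, the test and the sample-size SD do not refer clearly to one quantity, and the named test leaves the week-0 EASI unused as a covariate.

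Over r = 0.3 to 0.7, ANCOVA adds about 2 to 9 percentage points to the 90.4 % of the score comparison at 62 per group. Against an analysis of change it adds about 14 points at r = 0.3 (92.8 − 78.8) and under 1 point at r = 0.7. These sizes rest on the assumed r, on equal SDs at both times, and on the effect and SDs in the Sample size section. The direction does not depend on the exact r: apart from the lost degree of freedom, ANCOVA is at least as precise as either alternative.

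A reader might also want the age band that sets the dose as a factor. That is optional; the document shows no error that requires it.

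**What to change.** 1. Make the primary analysis an ANCOVA of week-12 EASI on treatment, with baseline EASI as covariate, and report the adjusted mean difference with its 95 % confidence interval. The treatment estimate is the same for score or change, so the outcome can still be described as change.
2. Analyse POEM and CDLQI in the same way, each with its own baseline.
3. Replace the switch to an unnamed nonparametric test with a baseline-adjusted analysis stated in advance, for example on a transformed scale or on ranks.
4. Recalculate the main-trial sample size from the pilot residual SD of this model, not from the unadjusted SD of the score. ANCOVA alone does not align the sample size with the analysis; this step does.

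The cost is a change of wording and one degree of freedom. The baselines are already scheduled at week 0, so no new data are needed.

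### The observed distribution decides whether the primary EASI test is ANOVA or a rank test, so the p value may not test the mean difference that the protocol reports and powers

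*Protocol article*

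**What the plan says.** The Statistical analysis section makes two statements about the same variables.

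- On the effect measure: "Comparison of means of continuous variables (i.e., EASI, POEM and CDLQI scores) will be expressed as differences in means", each with a 95% CI. Nothing limits this to data that look normal.
- On the test: "One-way analysis of variance will be used for normally distributed data", whereas "nonparametric tests will be used for skewed distribution data".

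Other sections show that this rule reaches the primary comparison. Under Outcome measures, "The primary outcome measure is change in clinical signs severity based on EASI score". Under the section on screening and endpoint, "The endpoint is set at visit 4 (week 12) of the trial period". The Sample size section plans on EASI means and SDs (7.4 ± 3.3 against 9.6 ± 4.1), 90% power and a "significance level of 0.05 (α) in a two-tailed test". Table 1 shows that EASI is also recorded at baseline.

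**The concern.** A rank test such as Mann-Whitney asks whether values in one arm tend to be larger than in the other. It does not ask whether the means differ. The protocol fixes the mean difference as the reported effect and powers the trial on it, then allows the p value to come from a test of something else, depending on the data.

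Two things are at stake for the primary outcome. The hypothesis under test is not settled before the data are seen. And the report could show a significant p value beside a CI for the mean difference that includes zero, or the reverse, with no rule saying which one decides.

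**Working it through.** **1. The plan's own figure is a comparison of means.** Inputs from the Sample size section: difference 9.6 − 7.4 = 2.2; SDs 3.3 and 4.1; two-sided 0.05; 90% power.

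- Pooled SD = √((3.3² + 4.1²)/2) = 3.72, and d = 2.2/3.72 = 0.591.
- Normal approximation: n = 2(1.960 + 1.282)²/0.591² = 60.1, so 61 per arm.
- Noncentral t: 61.1, so 62 per arm, which is the stated number.
- A rank test with relative efficiency 3/π (normal parent) would need 61.1/0.955 = 64.0, so 64 per arm.

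The stated 62 is therefore the t-test answer. It is reached before any allowance for dropout (62/0.9 = 68.9, so 69 with the stated 10%). That is a separate matter and does not affect this point.

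**2. How often the p value and the CI would conflict.** The article gives means and SDs only, so shape and switch rule have to be assumed. Switch: Shapiro-Wilk p < 0.05 in either arm leads to Mann-Whitney, otherwise ANOVA. Shapes with mean m and SD s: normal; gamma with shape (m/s)² and scale s²/m; lognormal with log variance ln(1 + (s/m)²). There were 10,000 simulated trials per case with 62 per arm, on EASI scores. A conflict is a trial in which the rank branch is taken and the rank p value and the mean comparison fall on opposite sides of 5%.

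Planning means and SDs (7.4 ± 3.3 against 9.6 ± 4.1):

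| Shape | Power, ANOVA | Power, rank | Conflict |
|---|---|---|---|
| Normal | 90.7% | 89.0% | 0.6% |
| Gamma | 90.5% | 89.5% | 4.0% |
| Lognormal | 90.6% | 93.0% | 4.9% |

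The primary outcome is change, so the exercise was also run on change scores: gamma week-12 scores as above, and an assumed gamma baseline with mean 12, SD 3.7 or 5, and correlation 0.3 to 0.7 (2,500 trials per case). The rank branch was taken in 22 to 55% of trials and conflict arose in 0.3 to 4.0%. A repeat gave about 21 to 55% and 0.5 to 4%. Taken together, conflict occurs in roughly 0.5 to 5% of trials.

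**3. Type I error.** Same distribution in both arms (mean 9.6, SD 4.1, 62 per arm):

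| Shape | ANOVA | Two-stage rule |
|---|---|---|
| Normal | 5.1% | 5.1% |
| Gamma | 4.6% | 4.6% |
| Lognormal | 4.9% | 5.4% |

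The simulation standard error is √(0.05 × 0.95/10,000) = 0.2 percentage points. The rule does not materially inflate type I error.

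**4. The rank branch is not a test of means.** With equal means (9.6) but the planning SDs, 3.3 against 4.1, the two-stage rule rejects in 6.3% (gamma) and 6.6% (lognormal) of trials. ANOVA rejects in 4.8% and 4.4%. This is not the no-effect case of a randomised trial, where both arms share one distribution. It shows only that the two branches answer different questions.

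**The case against.** **The conflict is partly a matter of reading.** The sentence on differences in means could describe only how results are given when means are compared, that is, in the ANOVA branch. The text does not expressly pair a rank p value with a mean-difference CI. This has some force. But the sentence lists EASI, POEM and CDLQI with no exception, and on the narrower reading the effect measure of the primary outcome would itself depend on the observed shape.

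**Detail may sit elsewhere.** The criterion for skewness and the name of the rank test are commonly left to an analysis plan, which is not shown. Their absence is not the fault. The stated rule is, and naming a rank test would not make it test a difference in means.

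**Deliberate test selection is unlikely.** An independent statistician does the analysis, and the Blinding and allocation concealment section withholds the code from data-analysis personnel. This stands. It limits choice driven by the result, but not the mismatch.

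**Stronger readings to avoid.** A reader might infer that the rank test would in practice be the primary test, because raw gamma scores trigger the assumed switch in about 89% of trials. The documents do not support this: the outcome is change, the rate falls to about 21 to 55% on simulated change scores and is about 10% for normal scores, and neither shape nor switch is given. A reader might also infer serious alpha inflation from cases with a much larger SD in one arm. The planning SDs are 3.3 and 4.1, nothing more extreme appears, and equal means with unequal spread is not the null of no effect. Nor is the switch worthless: in the lognormal case the rank test has 93.0 − 90.6 = 2.4 percentage points more power.

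**Conclusion.** The concern holds in a limited form. The protocol states a data-dependent choice of primary test beside a fixed mean-based effect measure and a mean-based sample size. If the rank branch is taken, the p value does not test the reported difference. The two would then conflict on significance in roughly 0.5 to 5% of trials; the low end is for normal scores and some change-score cases, the high end for lognormal scores.

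These figures rest on assumed shapes, an assumed Shapiro-Wilk switch and, for change scores, an assumed baseline distribution and correlation. Type I error is not materially affected when the arms share one distribution. The practical effect is modest, but it falls on the primary outcome and is easily removed.

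**What to change.** Prespecify one primary analysis that applies whatever shape is observed: the between-group difference in mean week-12 EASI, adjusted for baseline EASI by ANCOVA, with the 95% CI and p value from the same model. Use robust or bootstrap standard errors if residuals are skewed, and take the p value by the same method as the CI. Because baseline is in the model, analysing week-12 EASI or change from baseline gives the same treatment effect, so this respects the stated outcome. Keep one named rank test as a labelled sensitivity analysis that does not decide the primary result. Apply the same rule to POEM and CDLQI.

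The change is a few lines in the Statistical analysis section, with no new data, since baseline EASI is already collected. Even without adjustment, a mean comparison under the planning values has 90.4% power with 62 analysed per arm and 87.3% with 56 (62 × 0.9 = 55.8). The gain from adjustment depends on the baseline correlation, which the article does not give. The downside is a small loss of efficiency if EASI is heavily skewed, about 2.4 percentage points of power in the lognormal case above.
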